#### Statistical Analysis Statistical power and sample size

The study that used 2g/day of E-EPA reported a 9.3-unit difference between baseline and 4-week differences in placebo and active groups for the HDRS, this difference was statistically significant (p < 0.001) [5]. The standard deviation for the groups was 7.4 (the larger of the standard deviations). A sample size of 11 subjects per group provides 80% power with an alpha= 0.05, to detect the above difference in HDRS between the treatment and placebo group. A sample size of 18 subjects per group will provide power greater than 95% with an alpha= 0.05, to detect a difference of 500 units for IFN- levels between baseline and post-treatment levels. This assumes a standard deviation of 400 units and is based on the results of a study that reported a decrease in IFN- levels in MS patients with MDD from baseline values after 16-wks of either therapy based or medication based treatments for depression [8]. Assuming a dropout rate of 20% the sample size of 60 subjects, or 30 per group is also more than adequate to detect a treatment difference in IFN- levels produced from PBMC. The additional sample will provide additional power for the exploratory analyses using the regression analysis. We are using the MADRS as the primary outcome measure as it is highly correlated with the HDRS [26-28] and will be more sensitive to treatment change in patients with MS than the HDRS. As we expect MADRS scores to have a greater change with treatment than the HDRS, we are well powered with 60 subjects.

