# Product quality control

Nordic Naturals will supply the fish oil supplement. This company follows the FDA guidelines for Good Manufacturing Procedures and verifies product quality and label claim by in-house and outside lab analysis. The fish oil capsules are tested for contaminants (e.g. heavy metals), lipid oxidation, and for omega-3 fatty acid content.

Analysis of outcome variables

The major outcome measures in this study are the 3-month change in MADRS and IFN-. Initially we will compare the difference in MADRS scores, BDI scores, and IFN- levels between the fish oil and placebo groups using a two-sample t-test. In a more exploratory analysis, we will then assess whether the change in IFN- levels is correlated with the change in MADRS. To do this we will build a multiple regression model, where the predictors are the baseline MADRS or BDI and IFN- levels and the change in IFN- levels. We will additionally assess whether there is an interaction between baseline IFN- and fish oil supplementation by extending the above regression to include the interactions terms with fish oil. In order to control for potential confounders (specifically age, gender, education level, disability, and fatigue), variable selection schemes (all possible regressions using maximum R2 and backwards elimination of variable) will be used to determine if any of these potential confounders predict the dependent variable. If so, these potential confounders will be included in the regression models as covariates.

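### The IFN-gamma power claim (above 95% with 18 per group) uses a baseline-to-post-treatment decline where the planned test needs a fish oil versus placebo difference, so it is unsupported

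*Protocol*

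**What the plan says.** Protocol section D, *Analysis of outcome variables*, names the 3-month change in MADRS and in IFN-gamma as the major outcomes. It compares IFN-gamma "levels between the fish oil and placebo groups using a two-sample t-test".

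The section on statistical power and sample size then says of IFN-gamma: "A sample size of 18 subjects per group will provide power greater than 95% with an alpha= 0.05, to detect a difference of 500 units". It describes this difference as one in "levels between baseline and post-treatment levels" and adds: "This assumes a standard deviation of 400 units". The source is a study of MS patients with major depression, in which IFN-gamma fell "from baseline values after 16-wks of either therapy based or medication based treatments for depression". The section concludes that 30 per group, with 20% dropout, is more than adequate to detect a treatment difference in IFN-gamma.

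The protocol gives no expected IFN-gamma change on placebo and no expected between-arm difference. It does not say whether 400 is the SD of a level at one visit or of a change.

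**The concern.** The effect size and the test concern different quantities. A fall from baseline in treated patients includes everything that happens to them over the period: regression to the mean, general improvement, and the treatment itself. A two-sample test sees only the part by which fish oil exceeds placebo. The source treatments were also depression therapies, not fish oil added to a stable antidepressant.

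The protocol itself gives reason to doubt a flat placebo arm. It allows for responders (more than 50% improvement) in both arms. Its Background reports a correlation of .64 between baseline BDI and IFN-gamma in 14 subjects, citing the same study from which the 500 is taken. If mood and IFN-gamma move together, placebo patients who improve could also show a fall.

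The HDRS sentence just before uses the right kind of quantity: a difference between placebo and active groups in change from baseline, from a placebo-controlled omega-3 trial. Only the IFN-gamma sentence lacks a control arm.

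At stake is how the IFN-gamma result is interpreted in a pilot meant to inform a larger trial. A stated power above 95% suggests more certainty about a null result than the plan supports.

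**Working it through.** **Inputs from the protocol:** difference 500, SD 400, alpha 0.05, 18 per group; 30 per group with 20% dropout, so 30 × 0.8 = 24 completers per arm. Sidedness is not stated; two-sided is assumed. Power is from the noncentral t distribution.

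**1. Reproduce the stated figure.** For two samples the noncentrality is difference / (SD × √(2/n)).
- n = 18: 500 / (400 × √(2/18)) = 3.75 on 34 df, power 95.4%.
- n = 17: power 94.2%, so 18 is the smallest n above 95%.
- Variants at n = 18: normal approximation 96.3%, one-sided t 97.9%.

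For a within-group (paired) test the noncentrality is difference / (SD / √n).
- n = 18: 500 / (400 / √18) = 5.30 on 17 df, power 99.9%.
- Eleven subjects would already give 96.1%.

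Both tests exceed 95% at 18. The choice of 18 per group fits the two-sample calculation much better, with 500 entered as the between-arm difference.

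**2. Allow for change on placebo.** Suppose fish oil lowers IFN-gamma by 500. The net difference is then 500 minus the placebo decline. That decline is an assumption, because the protocol gives none. SD of change is taken as 400.

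| Assumed placebo decline | Net difference | Power, 18 per arm | Power, 24 per arm |
|---|---|---|---|
| 0 | 500 | 95.4% | 98.9% |
| 100 | 400 | 83.0% | 92.4% |
| 200 | 300 | 58.9% | 72.0% |
| 250 | 250 | 44.5% | 56.3% |

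With 24 per arm, the detectable between-arm difference is 330 units for 80% power (0.826 × 400) and 425 for 95% power.

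**3. Allow for the undefined SD.** If 400 is the SD at one visit and ρ is the correlation between visits, the SD of change is 400 × √(2(1 − ρ)).
- ρ = 0.5: 400 × √1 = 400, so step 2 applies unchanged.
- ρ = 0: 400 × √2 = 566, the largest value for a non-negative correlation. Power for a net 500 is 73% with 18 per arm and 85% with 24. The detectable difference at 80% power with 24 per arm is 0.826 × 566 ≈ 467.
- ρ = 0.75: 400 × √0.5 = 283. The detectable difference falls to 0.826 × 283 ≈ 234.

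**The case against.** The strongest reply is that the calculation is correct and matches the planned test. Two samples, 500/400 and 18 per group give just over 95%. The sentence may be a loosely worded between-arm difference in change, as in the HDRS sentence before it. This stands in part: there is no arithmetic error, and a reader should not infer one. But loose wording does not supply the missing input, because the cited source is described only as a decline from baseline under treatment.

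A second reply is that little placebo change is plausible. Antidepressant and MS drugs must be stable at entry, and participation stops if the MS drug is changed or the antidepressant is changed or increased. That makes the assumption reasonable to consider, but the protocol should state it.

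A reader might go further and infer that the trial is underpowered for IFN-gamma. The protocol does not support that. With an SD of change of 400, 24 per arm keep 95% power down to a difference of 425 and 80% down to 330. If fish oil lowers IFN-gamma by 500, placebo could therefore fall by about 500 − 330 = 170 units before power drops below 80%. The low figures in the table rest on placebo declines that appear nowhere in the protocol. An SD of 566 needs uncorrelated visits, and a correlation above 0.5 would raise power.

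A reader might also take this as a flaw in the sample size of 60. It is not: MADRS is the primary outcome measure, and IFN-gamma belongs to Aim 2, the secondary objective, although it is also listed as a major outcome. Nor does the protocol say that it would read a null IFN-gamma result as evidence against the mechanism. That is a risk of the wording, not a stated plan.

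**Conclusion.** The point holds as one about an unsupported input. Power above 95% for the planned IFN-gamma test requires the full 500-unit decline to be a net difference from placebo, and 400 to be the SD of the 3-month change. Neither is stated, so neither the power figure nor the adequacy claim is supported.

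How far true power departs from 95% cannot be determined from the protocol. Over the assumed range of net differences from 500 to 250, at 24 completers per arm and SD of change 400, it runs from 99% to 56%. For a net 500 with uncorrelated visits and a single-visit SD of 400, it is 85%. All figures assume a two-sided 0.05 test and 20% dropout. The weight is moderate: a named major outcome, but one that serves a secondary aim and does not drive the sample size.

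**What to change.** Replace the IFN-gamma power sentence with a detectable difference, for example: *With 24 completers per arm, the two-sample t-test at two-sided 0.05 has 80% power for a between-arm difference of about 330 units in the 3-month change in IFN-gamma, if the SD of that change is 400.*

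State whether 400 is the SD of a change or of a single-visit level. If it is a single-visit SD, give the assumed correlation between visits; the detectable difference is then up to about 467 units when visits are uncorrelated. Delete the statement that 30 per group is more than adequate for IFN-gamma.

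The cost is wording only. The test, the visits and the number of patients stay as they are; the protocol gives up the stated power above 95%.

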#### Randomization

After study eligibility is established subjects will be randomized to placebo or fish oil supplementation by using a computer-generated scheme. Because of sample size limitations we will only stratify on one parameter prior to randomization, which will be the BDI score at screening. Subjects will be stratified into two categories “mildly depressed” with BDI scores 10-17 and “moderately depressed” with BDI scores 18-30. This will insure that each group will contain equal numbers of mild and moderately depressed subjects. The data management coordinator that is in charge of labeling medication will maintain the randomization list.

#### Compliance and Adverse Events

Compliance will be measured by pill count and RBC fatty acid analysis. Refer to section E. Human Subjects, “protection against risks”, p. 14 for monitoring of adverse events.

Blinding, Data Collection and Management

Refer to section E. Human Subjects, “sources of material”, p. 13.

**Assessments**

Beck Depression Inventory (BDI)

The BDI is a 21-item self-report measure of depression [30] and is commonly used in MS studies [7, 8, 22, 31, 32]. It is an easily administered measure for depression that is not clinician-dependent. We will examine how well the BDI scores correlate with clinician rated scores of depression ( MADRS).

Structured Clinical Interview for DSM-IV (SCID)

The SCID is a semi-structured interview that can be administered by a well-trained clinician or research associate. It is designed to assess major Axis I disorders [31] and will be used to assess MDD at screening and after 3 months and 6 months on supplementation.

The Montgomery-Asberg Depression Rating Scale (MADRS)

The MADRS is a structured interview assessment of depression, designed to be especially sensitive to changes in patients’ depression symptoms after antidepressant therapy [48]. The MADRS scale is more oriented towards psychic rather than somatic symptoms of depression [47].

Expanded Disability Status Scale (EDSS)

The EDSS is an ordinal scale giving a measure of neurological impairment on a scale between 0 (normal) to 10.0 (dead). Patients with scores in the .5-4.0 range have mild disability and are able to walk at least 500 meters without aid or rest. Patients with scores of > 7.5 are cannot walk and have upper extremity dysfunction [32].

Multiple Sclerosis Functional Composite (MSFC)

The MSFC includes measurements of ambulation (timed 25 foot walk), upper extremity function (nine hole peg test) and cognitive performance (PASAT III) [33]. It is an objective measure of disability and is often used in MS studies along with the EDSS to evaluate treatment effect on disability.

Mini-Mental State Exam (MMSE)

The MMSE is among the most widely used screening instruments for cognitive impairment indicative of dementia[34]. This 30-point scale is helpful for comparing across diverse studies as it has become a common way of assessing severity of dementia among clinicians. Any subject that scores 24 or less on the MMSE indicates a mild to severe forms of dementia. As dementia can significantly affect depression scores we will screen for and exclude subjects with dementia.

Multiple Sclerosis Quality of Life Inventory (MSQLI)

The MSQLI is a modular MS-specific HRQL instrument consisting of the SF-36 and supplemented by nine symptom specific measures (fatigue, pain, bladder function, bowel function, emotional status, perceived cognitive function, visual function, sexual satisfaction, and social relationships). The reliability and construct validity of this measure has been evaluated by a field test of MS patients with a broad range of disability (EDSS 0-8.5), and its content has been validated by MS specialists (neurologists and allied health professionals), HRQL experts, patients and caregivers [35]. A modified version of the FIS is incorporated into the MSQLI. The FIS is a well-validated measure of fatigue[36, 37].

#### Block Food Frequency Questionnaire

The Block food frequency questionnaire [38]. This 147-item instrument is based on extensive population surveys validated by food records.

#### RBC fatty acid

RBC analysis is a quantitative measure of the incorporation of fatty acids into cell membranes. This assay will be performed in the Lipid laboratory at OHSU. These methods have been validated and previously published [39, 40].

#### Peripheral Blood Mononuclear Cell (PBMC) Separation

PBMC will be isolated from heparinized blood within 4 hours of blood draw (Ficoll Hypaque; Pharmacia Biotech, Uppsala, Sweden). This method of separation has been described in previously published reports [41, 42]. Separated PBMCs will be stored at –80C for cytokine measurement. PMBCs will also be frozen and stored for future testing of gene expression by microarray assay.

#### Stimulation of PBMC

PBMC will be stimulated with a mitogen (Concanavalin A). One ml of freshly isolated PBMC suspension will be added to each well. Cells will be cultured for 48 hours at 37C and 7% CO2, after which time cultures will be clarified by centrifugation and supernatants were aliquoted and frozen at –80C until used for cytometric bead array analyses.

#### Cytokine measurement

Cytokine levels from unstimulated and stimulated PBMC will be measured using the Cytometric Bead Assay (CBA, BD Biosciences, Pharmigen). The company reports good intra- and inter- assay reproducibility for all cytokines measured: Intra-assay %CV < 5.0; Inter-assay % CV (< 80 pg/ml) < 11.0; Inter-assay %CV (625-2500 pg/ml) < 6%. The CBA kit was chosen to measure cytokines because it a reliable, precise, and economical method for measuring an array of human cytokines in a single sample.

#### Other laboratory tests

Comprehensive metabolic panel that includes liver function tests and prothrombin time will be determined in the laboratory at OHSU. We will use these measures along with reports of adverse events to monitor treatment safety. Matrixmetalloproteinase-9 levels from stimulated PBMC will be measured by ELISA, as they mediators of the inflammatory process by allowing inflammatory cells into cross the blood brain barrier.

# E. HUMAN SUBJECTS

1. ***Human Subjects Involvement and Characteristics***

A total of 60 subjects will be enrolled in this trial. We will select subjects with relapsing remitting MS that have mild to moderate depression. Women and members of minority groups will be included.

#### **Inclusion Criteria**

-Definite MS by McDonald criteria [25]

-Relapsing remitting course of MS

-Meets DSM-IV criteria based on SCID for Axis I disorders [31]

-Age 18 or older

- Scores between 11-30 on the MADRS (indicating mild to moderate depression) [26]

-Scores 25 or greater on the MMSE

-no essential fatty acid supplementation and < 6 oz per week of fish in diet at least 1 month prior to enrollment

-on stable dose of anti-depressant medication (no change in medication or dose at least 3 months prior to enrollment)

-on stable dose of interferon beta or glatiramer acetate (no change in MS disease modifying medication at least 6 months prior to enrollment)

-Able to understand and sign consent

#### **Exclusion Criteria**

-Severe depression with suicidal ideation and plan as determined by SCID >20 and MADRS > 30

-Serious psychological disorders (e.g. psychotic disorders, bipolar disorder)

-Taking 2 or more antidepressants

-Plans to change antidepressant therapy within 3 months of enrollment

-Serious medical conditions such as congestive heart failure, cancer, liver disease, kidney failure.

-Current or past history of clinically significant ventricular arrythmias: includes patients that are receiving implantable cardioverter defibrillator (ICD) for sustained ventricular tachycardia (VT) or ventricular fibrillation (VF), or patients that had received an ICD or ICD therapy for an episode of VT/VF within the past 6 months, or subjects currently taking anti-arrythmia medications for VT/VF (e.g. Quinidine, Amiodarone).

-MS exacerbation or corticosteroid treatment 1 month prior to enrollment

-Pregnancy (pregnancy might alter results on outcome measures)

-Enrolled in another study

Because of the short duration of this study, subject participation will be stopped for the following reasons: MS exacerbation, change in MS disease modifying medication, and change or increase in antidepressant medication.

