Our primary objective, Aim 1, is to determine the treatment effect on depression by using the MADRS and BDI. We will also monitor adverse events by subjects self-report of general health and laboratory tests (metabolic panel, including liver function tests and prothrombin time). We will monitor worsening of depression and suicidal ideation using both depression inventories, BDI and MADRS. Our secondary objective, Aim 2, is to determine the treatment effect on inflammatory cytokine levels, as fish oils may exert its clinical effect by decreasing peripheral levels of proinflammatory cytokines. We will measure cytokines released from mitogen stimulated peripheral blood mononuclear cells (PBMCs) by immuno-assay. Compliance will be monitored by pill count and red blood cell fatty acid analysis. Data collected from this pilot study will be used to aid us in the design of a larger, multi-center clinical trial that could more fully evaluate the effectiveness of this therapy.

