#### Visit 1 (Screen)

The screening visit is to establish eligibility for study participation. This visit and all subsequent visits will take place at the MS Center of Oregon at OHSU or at the General Clinical Research Center (GCRC) at OHSU. Each potential study subject will be consented at this visit after which a family and medical history will be taken. The subject will be screened for major depressive disorder using the SCID, dementia by the MMSE, and for mild to moderate depression using the MADRS. They will then be asked to fill out the BDI. Concomitant medications will also be recorded at the screening visit (*See Table 1: Study Schedule: Phase I*).

Visit 2 (Baseline)

Subjects that meet study inclusion after the screening visit will be scheduled for follow up within 2 weeks. At this visit subjects will receive a brief physical exam and a neurological exam (EDSS) from [name]. The subject will be given a MADRS score. A research assistant will administer the MS Functional Composite (MSFC) and record concomitant medications. The subject will fill out study questionnaires which include: BDI, Multiple Sclerosis Quality of Life Inventory (MSQLI), and Food Frequency. A research assistant will draw blood for cytokine levels, prothrombin time (PT/INR), comprehensive metabolic panel, and RBC fatty acid analysis.

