#### Visit 3 (day 0)

#### This visit will occur one week after baseline. At this visit, subjects will receive study medication for 1 month and be instructed on the dose.

#### Visit 4 (week 2)

At this visit subjects will be screened for worsening of depression (>30 on the BDI) and suicidal ideation using question #9 from the BDI. If either of these occurs the subject will be immediately referred for standard care and will be exited from the study. General health adverse events will also be recorded at this visit. [name] will be available by pager 24 hours a day to address patient safety issues. [name] will be available to discuss these cases with [name]. The subject will be instructed to bring their medication bottle to their next scheduled visit.

Visit 5 (week 4)

All measures except PE/neurological exam/EDSS, the Food Frequency questionnaire, and the MSFC will be assessed at this visit. A research assistant will draw blood for prothrombin time (PT/INR), comprehensive metabolic panel, cytokine levels, and RBC fatty acid analysis. A research assistant will assess the subject for adverse events and perform a pill count. The subject will also be asked about any changes in medication or doses of medications (prescribed and over the counter). The subject will be instructed to bring their medication bottle to their next scheduled visit.

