The Data Safety and Monitoring Board of ORCCAMIND will monitor this study to ensure the safety of subjects. We will monitor adverse events by laboratory tests, which include prothrombin time (PT/INR) and comprehensive metabolic panel. For the first month of the study general health events, worsening of depression (>30 on BDI), and suicidal ideation (question # 9 on BDI) will be monitored weekly (2 x by phone and 1x in-clinic) for all subjects. If either of these occurs the subject will be immediately referred for standard care and will be exited from the study. [name] will be available by pager 24 hours a day to address patient safety issues. [name] will be available to discuss these cases with [name]. After the first month, subjects will be monitored every other week for general health events, worsening of depression (>30 on BDI), and suicidal ideation (question # 9 on BDI) (1 x by phone and 1x in-clinic). The same procedures described for month-1 will apply for all subjects throughout the study period. Subjects that have an acute MS exacerbation during the study will be referred to their neurologist for care.

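### The entry criteria do not match the protocol's own safety exit rule: suicidal ideation on BDI item 9, or a Visit 2 BDI above 30, has no written consequence before capsules are dispensed

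*Protocol*

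**What the plan says.** **Entry.** The Inclusion Criteria set severity by the MADRS alone: "Scores between 11-30 on the MADRS (indicating mild to moderate depression". Neither eligibility list mentions the BDI or its item 9. The one exclusion that touches suicidality is "Severe depression with suicidal ideation and plan as determined by SCID >20 and MADRS > 30".

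**Before dosing.** The BDI is completed at Visit 1 and Visit 2. Eligibility is treated as settled after Visit 1: "Subjects that meet study inclusion after the screening visit will be scheduled for follow up within 2 weeks". At Visit 2 the BDI is one of several questionnaires, with no action tied to its score. Visit 3 follows one week later: "At this visit, subjects will receive study medication for 1 month and be instructed on the dose". Table 1 schedules neither BDI nor MADRS at Visit 3.

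**Randomization.** The section of that name stratifies on screening BDI, 10-17 against 18-30.

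**After dosing.** At Visit 4 subjects are "screened for worsening of depression (>30 on the BDI) and suicidal ideation using question #9 from the BDI". The section on protection against risk gives the same two triggers and the consequence: "If either of these occurs the subject will be immediately referred for standard care and will be exited from the study". It then adds: "The same procedures described for month-1 will apply for all subjects throughout the study period". The abstract says of monitoring: "We will monitor worsening of depression and suicidal ideation using both depression inventories, BDI and MADRS".

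**The concern.** The protocol judges that a subject with item 9 ideation, or a BDI above 30, should be referred at once and leave the study. It applies that judgement only once capsules have been handed out, although the same questionnaire is completed twice beforehand. Followed to the letter, the plan can enrol and dose a subject in a state that it treats as a reason for exit.

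Two things are at stake. The first is safety: ideation recorded at Visit 1 or 2 triggers no written referral. The second is avoidable loss: a subject exited at weeks 1 to 3 contributes no on-treatment value of the primary depression measure.

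**Working it through.** **1. What the exclusion removes.** Inclusion requires MADRS 11-30. The exclusion, read literally, requires MADRS above 30. The two sets do not overlap, so the exclusion adds nothing. Its other cut-off, a SCID score above 20, has no meaning in this document, because the Assessments section describes the SCID as a semi-structured interview and gives it no score. On the loosest reading (ideation with a plan, at any MADRS), ideation without a plan is still admitted.

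**2. Where the exit rule applies in Phase I (Table 1, BDI row).**
- Before dosing: Visits 1 and 2, so 2 administrations. Exit rule written for 0 of 2.
- After dosing: weeks 1, 2, 3, 4, 8, 10 and 12, so 7 administrations. Exit rule applies at 7 of 7.

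These counts describe the schedule; they do not measure an effect.

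**3. Timing.**
- Visit 2 to Visit 3 is 1 week, and Visit 3 to the first exit check is 1 week: 1 + 1 = 2 weeks from the last pre-dose BDI to the first check.
- On-treatment MADRS falls at weeks 4, 8 and 12. Three exit checks (weeks 1, 2 and 3) come before the first of these.

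**4. Two illustrative subjects, other criteria assumed met.**

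| | Main case | Narrow case |
|---|---|---|
| MADRS | 25 | 28 |
| Screening BDI | 24 | 29 |
| Stratum | 18-30 | 18-30 |
| Pre-dose state | item 9 ideation, no plan | Visit 2 BDI of 32 |
| Excluded by a written rule? | No | No |
| Dosed at Visit 3? | Yes | Yes |
| Week 1, if the state persists | meets the item 9 trigger, subject to its undefined threshold | meets the BDI trigger, if above 30 is an absolute level |

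If the exit rule instead means new onset, the main-case subject is dosed and kept on study with no referral rule. The gap changes form but stays open.

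**5. Effect on stated power.** The plan's own figure is 11 per group for 80% power at alpha 0.05, with difference 9.3 and SD 7.4 on the HDRS. Standardized difference = 9.3 / 7.4 = 1.26. A two-sided two-sample t-test needs 10.99, so 11 per group, with power 0.8005. The figure reproduces.

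With the planned 20% dropout, 30 × 0.80 = 24 per group, giving power 0.989. No rate for the extra exits is given, so a range is assumed on top of that dropout:

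| Further loss | n per group | Power (9.3 / 7.4) |
|---|---|---|
| 0% | 24.0 | 0.989 |
| 10% | 21.6 | 0.981 |
| 20% | 19.2 | 0.966 |
| 30% | 16.8 | 0.942 |

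For interferon gamma the plan asks for 18 per group. The margin is 24 − 18 = 6 per group, or 6 / 24 = 25% of those remaining.

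**The case against.** **The BDI is limited before dosing.** This stands for the screening score. Strata exist only for 10-17 and 18-30, so a subject screening above 30 cannot be randomized as written. A reader might infer that no BDI limit of any kind applies before dosing; the Randomization section does not support that. The strata are nonetheless not an eligibility criterion, they use the screening score only, and they say nothing about item 9 or the Visit 2 BDI.

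**The BDI trigger is about worsening.** This stands in part. A subject at 32 before dosing and 32 at week 1 has not worsened since dosing, so exit is not certain. The parenthesis gives an absolute level and no baseline comparison, which makes exit the more literal reading. The case is also narrow: it needs MADRS within 11-30, a screening BDI of 30 or below, a rise past 30 by Visit 2, and persistence.

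**The item 9 threshold is undefined.** This also stands. A reader might infer that any subject with a positive item 9 before dosing will certainly be exited. The protocol does not say which response counts, so that cannot be shown.

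**Clinicians see the subject before dosing.** The MADRS is done at Visits 1 and 2, the SCID at Visit 1 and an examination at Visit 2. Staff may well act on what they find, but no written action follows. The sentence extending the month-1 procedures to the whole study period comes after the on-treatment contact schedule and sets no pre-dose check.

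**Admitting ideation without a plan may be deliberate** in adults with major depression who have weekly contacts in month 1. If so, requiring exit for that same ideation once capsules are dispensed is hard to reconcile with it.

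**Conclusion.** The mismatch is real and should be fixed. The suicidality exclusion does no work as written, and no written rule acts on item 9 at Visits 1 and 2, or on the Visit 2 BDI, before dispensing. The item 9 case is the main one. The Visit 2 BDI case is secondary and rests on reading the limit of 30 as an absolute level. In both, exit at weeks 1 to 3 depends on the state persisting.

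How many subjects this touches cannot be determined. The protocol gives no item 9 data, and the BDI data in its Preliminary Studies section come from subjects not described as selected by SCID or MADRS.

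A reader might infer that the sample size or the main comparison is undermined. The document does not support that. On the plan's own HDRS assumptions, power stays above 0.94 even with a further 30% loss. The states in question arise before dosing in a double-blind randomized trial, and nothing here makes the two-sample t-test invalid. The consequence is a safety inconsistency with some avoidable early loss.

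**What to change.** 1. **Visit 4 and the section on protection against risk:** state which item 9 response counts as ideation for exit.
2. **Eligibility:** exclude subjects who meet that same item 9 definition, or who have a BDI above 30, at Visit 1 or Visit 2. Check both scores before dispensing at Visit 3, and complete the check before randomization. Refer those screened out to standard care, as is already done after dosing.
3. **Exclusion Criteria:** rewrite the suicidality line so that it does not depend on MADRS above 30, and delete the SCID cut-off.
4. **Inclusion Criteria:** write in the screening BDI range of 10-30 that the strata imply. At present a subject with MADRS 11-30 and a BDI outside that range meets the listed criteria but has no stratum.

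**Cost.** A protocol amendment and a check of questionnaires already completed at Visits 1 and 2; no added assessment. The real price is in recruitment. An unknown number of otherwise eligible subjects would be screened out. Those whose state persisted would meet the exit rule anyway if it is read as an absolute level; those whose state would have resolved by week 1 are lost only because of the change. The sponsor controls part of this price through where it sets the item 9 threshold, provided entry and exit use the same one.
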